## Abstract

Systemic lupus erythematosus (SLE) is a complex autoimmune disease that affects multiple organs and systems with a broad and heterogeneous spectrum of clinical manifestations. National disease-specific datasets and registries are crucial for clinical research since they can provide real-world and long-term data about clinical aspects, biomarkers, and treatments. Registries collect data from actual patients over time, outside the controlled environment of randomized controlled trials. This can help enhance the understanding of the natural history of a disease, provide information about how treatments work in everyday settings and elucidate potential variations in care and outcomes across different geographic areas. Here, we present a protocol for the creation of a standardized national disease-specific dataset for patients with SLE—the Systemic Lupus Erythematous Network (LUNET) Registry—which will facilitate data sharing, cross-comparison, and interoperability among centers. The LUNET registry is intended to serve as a comprehensive primary data source, capturing real-world longitudinal clinical information and the heterogeneity of patient presentations that are often underrepresented in traditional clinical trials. Ultimately, the LUNET registry will help to optimize SLE management in routine clinical practice by enabling the compilation of real-world evidence to inform clinical decision-making and health policy.

## 1. Introduction

Systemic lupus erythematosus (SLE) is a chronic autoimmune disease characterized by immune system dysregulation [1,2]. The presentation includes a broad and heterogeneous spectrum of clinical manifestations that can affect several organ systems and that pose substantial morbidity and mortality risk [3]. Preventing long-term organ dysfunction requires early diagnosis, along with prompt and targeted treatment. Due to the multisystemic nature of SLE, case management should entail a multidisciplinary approach that integrates expertise from different specialists [3]. To support early diagnosis and assessment of disease activity, recent studies have investigated several biomarkers that seem promising based on our improved understanding of the pathogenic mechanisms underlying SLE development [4,5]. Additionally, in recent years, the therapeutic armamentarium has substantially broadened. Notably, biological-targeted drugs (i.e., belimumab and anifrolumab), together with conventional disease-modifying antirheumatic drugs (cDMARDS), have enabled improved management of SLE patients, with treatment tailored according to their clinical phenotypes [5,6]. In this era of precision medicine, it is increasingly important to perform early patient characterization based on clinical and laboratory features, thereby enabling prediction of long-term prognosis and therapeutic outcomes [7].

The greater availability of effective and safe drugs has significantly increased patients’ survival; however, mortality remains higher among patients with SLE compared to in the general population, and new causes of death have emerged, which must be further explored to improve prevention strategies [8]. Moreover, certain clinical manifestations associated with specific organ involvement—e.g., neuropsychiatric systemic lupus erythematosus (NPSLE)—have not yet been fully characterized, due to the heterogeneity of definitions and study populations in the existing literature [9,10,11]. In the present paper, we describe a protocol for the establishment of a standardized national disease-specific dataset for patients with SLE—the Systemic Erythematous Lupus Network (LUNET) Registry—which will facilitate data sharing, cross-comparison, and interoperability among centers. The LUNET project is designed to provide high-quality, robust data to enhance our comprehension of SLE, evaluate the short and long-term safety and effectiveness of various treatment approaches, and globally improve SLE patient management in the real-life setting.

The primary objective of this initiative is to establish a national disease-specific dataset, designed to collect comprehensive clinical information from the largest feasible cohort of patients with SLE. This resource will support robust statistical analyses, and promote the integration of evidence-based findings into routine clinical practice. We primarily aim to gather real-world data from as many patients as possible in order to describe the different clinical presentations of SLE in the Italian population. This will expand the current knowledge regarding SLE clinical variability and possible presentations in a manner that will be more efficient and provide more detailed information, compared to traditional clinical research, which often relies on single-center data. Our specific objectives are as follows:Planning and conducting epidemiological studies to evaluate the incidence and prevalence rates of different clinical manifestations of SLE, and to evaluate short- and long-term outcomes, including survival rates and organ dysfunction, injury, and failurePromoting multicenter studies that will compare different patient subgroups based on clinical phenotypes and organ involvement, to attain insights regarding disease expression and progressionDescribing the profile of patients with lupus nephritis in the national population, to improve guidelines on its systematic and standardized assessment.Evaluating the presence of central and peripheral nervous system involvement in the national population of patients with SLE, assessing the type, frequency, and severity of neurological symptoms and objective signs, as well as the instrumental techniques used in clinical practice (e.g., Magnetic Resonance Imaging (MRI)Assessing biomarker data to support early diagnosis and guide treatment choicesImproving screening techniques for early identification of organ damage in SLE patientsImproving early treatment strategiesTracking adherence and response to therapyEvaluating the short- and long-term real-life effectiveness and safety of old and novel drugs approved for SLE, overall and in groups of patients with specific phenotypesAssessing SLE patients’ quality of life according to clinical phenotype and treatment approachAssessing how socioeconomic status impacts patients’ access to healthcare and absenteeism in relation to the disease and various therapeutic approachesEvaluating how different therapeutic strategies impact hospitalizationAssessing the influence of old and novel therapies on fertility, pregnancy, and breastfeedingMonitoring cardiovascular risk in SLE patients by evaluating the associated comorbidities, prospective development of cardiovascular events, and biomarker levels (e.g., fasting blood glucose, hemoglobin A1c, total cholesterol, HDL cholesterol, LDL cholesterol, triglycerides and pro-BNP)Evaluating bone metabolism in patients with SLE through assessment of laboratory measurements (e.g., vitamin D, calcium, phosphorus, calciuria, and phosphaturia) and instrumental assessments, such as dual-energy X-ray absorptiometry (DEXA) scansMonitoring the causes of death among SLE patients

Here, we describe the LUNET protocol, which was designed to characterize and manage the heterogeneity of SLE pathology. The primary outcome was defined as the incidence and prevalence rates of various clinical manifestations of SLE. The clinical spectrum of SLE in the national population will be comprehensively assessed, including both frequent and rare manifestations, in recognition of the disease’s multisystemic nature. Particular focus will be placed on lupus nephritis and neuropsychiatric involvement, given their role as key indicators of disease severity and their impact on prognosis. Given this largely descriptive primary objective, we will evaluate the adequacy of the sample size over the course of the study, with consideration of both the quantity and quality of the collected data.

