### 2.2. Oversight

The LUNET Study is overseen by three governing bodies: the LUNET Steering Committee (SC), the LUNET Scientific Committee (SciC), and the Publication and Dissemination Committee (P&DC) (Figure 1).

The LUNET Network currently comprises 18 centers across Italy, and involves leading experts in clinical immunology, internal medicine, and rheumatology (Figure 2).

The LUNET Network remains open to the inclusion of additional centers to continuously expand the dataset and improve the representativeness of its real-world clinical evidence. The primary requirement for participating centers is a specific expertise in diagnosing and managing SLE patients. Specific selection criteria include: access to an active cohort of patients with SLE sufficient to ensure regular enrollment and follow-up; availability of qualified personnel such as clinical investigators and research nurses; a dedicated outpatient clinic for systemic autoimmune diseases; access to biotechnological and investigational drugs; Day Hospital/Day Service activities; ward support for standard inpatient admissions and/or dedicated beds; and availability of instrumental diagnostics (e.g., capillaroscopy, spirometry, ultrasound, renal biopsy, etc.).

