### 2.3. Patients

Patients will be enrolled from the Italian Referral Center of Clinical Immunology, Rheumatology, and Internal Medicine, which has specific expertise in SLE management. The registry will enroll consecutive patients, who must meet all of the following inclusion criteria: age ≥ 18 years; confirmed SLE diagnosis according to the SLICC 2012 [1] and/or ACR/EULAR 2019 classification criteria [2]; and provision of signed written informed consent prior to participation. Written informed consent will be obtained after participants are given a comprehensive explanation of the registry’s objectives, emphasizing that participation will not influence clinical management or treatment. Participants will be informed of their right to withdraw consent at any time without repercussion, and will be assured that all data will be handled in compliance with applicable laws, to ensure privacy, pseudonymization, and data security. Once the inclusion criteria are fulfilled, no exclusion criteria will preclude the patients’ enrollment.

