## 4. Conclusions

National and international disease registries and networks have played pivotal roles in advancing our understanding of heterogeneous diseases, such as SLE. The LUNET project is intended to serve as an active primary source of real-world data about SLE patients across Italy and to support clinical research by providing long-term insights and capturing diverse patient experiences that are often underrepresented in traditional clinical trials. Unlike initiatives focused on specific disease aspects, the LUNET registry is designed to collect comprehensive data about clinical manifestations, therapeutic interventions, and outcomes, thereby facilitating the development of personalized treatment strategies grounded in real-world evidence. Furthermore, the broad geographic coverage of the registry will help standardize data collection across regions, reduce variability, minimize bias, and ensure sufficient statistical power to address a wide range of clinical and research questions. The LUNET registry is not only comprehensive but also innovative in its scope and real-time data collection, which allows for more accurate monitoring of disease progression and treatment effectiveness in everyday clinical practice. This represents a crucial step forward in bridging the gap between clinical trials and real-world patient management. For clinicians, the registry provides actionable insights that can inform tailored treatment decisions, optimize patient outcomes, and enhance the overall quality of care. By capturing longitudinal data across diverse patient populations and healthcare settings, LUNET empowers healthcare providers with evidence-based tools to better anticipate disease flares, manage comorbidities, and personalize therapeutic approaches in SLE. Ultimately, the establishment of this national network will foster international collaboration, enabling the identification of shared and divergent disease patterns and contributing to improved global management of this highly heterogeneous condition.

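### Aim and primary rates are stated for the national SLE population, but only adults with classified SLE at expertise-selected referral centres are sampled, with no non-SLE comparators for the early-diagnosis objective

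*Protocol article*

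**What the plan says.** **Target.** The Introduction says data will be gathered "in order to describe the different clinical presentations of SLE in the Italian population". The specific objectives on lupus nephritis and on nervous-system involvement are also set in the national population. The outcome is then fixed: "The primary outcome was defined as the incidence and prevalence rates of various clinical manifestations of SLE". The next sentence reads: "The clinical spectrum of SLE in the national population will be comprehensively assessed, including both frequent and rare manifestations".

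**Who is enrolled.** Section 2.3 states: "Patients will be enrolled from the Italian Referral Center of Clinical Immunology, Rheumatology, and Internal Medicine, which has specific expertise in SLE management". It continues: "The registry will enroll consecutive patients, who must meet all of the following inclusion criteria: age ≥ 18 years". The other two criteria are a "confirmed SLE diagnosis according to the SLICC 2012" and/or ACR/EULAR 2019 criteria, and written consent. There are no further exclusions.

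**Which centres.** Section 2.2 (Oversight) lists 18 centres. The main requirement is expertise in SLE. Further criteria include "a dedicated outpatient clinic for systemic autoimmune diseases; access to biotechnological and investigational drugs", day-hospital activity, inpatient support and diagnostics such as renal biopsy. The network may add centres, and the article expects this to improve representativeness.

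**What is claimed.** The Conclusions say that broad geographic coverage will help standardise data collection and will "reduce variability, minimize bias, and ensure sufficient statistical power to address a wide range of clinical and research questions".

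**Biomarkers.** One specific objective is to assess biomarker data in support of early diagnosis and treatment choice. A separate objective concerns early identification of organ damage in SLE patients.

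**The concern.** The population named in the aim is wider than the population that can enter the registry. Adults followed only outside such centres, and everyone under 18, cannot be enrolled. The article mentions no weighting or external calibration to bridge the gap.

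The stated uses make this matter. The nephritis objective is meant to improve guidelines on assessment, and the Abstract says the evidence should inform health policy. A prevalence reported under the present wording would be taken as a figure for Italian SLE patients.

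The early-diagnosis objective raises a separate difficulty. A marker that supports diagnosis has to separate people with SLE from people who might have it and do not. The registry enrols nobody in the second group.

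This is not a detail that a condensed article leaves to a fuller document, because the article itself fixes both the target population and the eligibility criteria.

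**Working it through.** The article gives no sample size, referral fraction, severity mix or expected rate, so there is no planned figure to reproduce. The check compares target with sampling frame and then illustrates what selection can do.

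**1. Target against frame**

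| Element | Target (Introduction) | Frame (sections 2.2, 2.3) |
|---|---|---|
| Place of care | Italy | Expertise-selected referral centres |
| Age | No limit stated | 18 or over |
| Disease status | SLE | Already meets classification criteria |
| Selection within centre | – | Consecutive, consenting |

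Consecutive enrolment without exclusions limits selection within a centre. It has no effect on which patients reach that type of centre. A new centre must meet the same main requirement, and a new region adds patients of the same type of centre, so neither removes the selection.

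**2. Effect of selection (all inputs assumed)**

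Let p be the prevalence of a manifestation among all Italian SLE patients. Let r be the probability of being followed at a network centre with the manifestation, divided by that probability without it. Then

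registry prevalence = r·p / (r·p + 1 − p).

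Example: p = 0.30 and r = 1.25 give 0.375 / (0.375 + 0.70) = 0.349.

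| r | p = 30% | p = 10% |
|---|---|---|
| 0.8 (reverse) | 25.5% | 8.2% |
| 1 (none) | 30.0% | 10.0% |
| 1.25 | 34.9% | 12.2% |
| 1.5 | 39.1% | 14.3% |
| 2 | 46.2% | 18.2% |
| 3 | 56.2% | 25.0% |

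The result depends entirely on r, which the article does not give.

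**3. Does size help?**

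At a prevalence of 30% the 95% half-width is 1.96·√(0.3·0.7/N): 4.0 points at N = 500, 2.8 at N = 1,000 and 1.4 at N = 4,000. With r = 1.25 the interval is centred on 34.9%. Put d = (0.349 − 0.30)/√(0.349·0.651/N). The chance that the interval contains the national 30% is Φ(1.96 − d) − Φ(−1.96 − d): about 37%, 10% and 0% at the three sizes. With r = 1 it stays at 95%. A larger registry narrows the interval without moving its centre.

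**4. Power claim**

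The Introduction leaves adequacy of the sample size to be judged during the study. Section 2.6 defers sample size and power to each later registry study. No number or precision target stands behind the assurance in the Conclusions.

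**5. Early diagnosis**

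Non-SLE participants number 0 by design, so true negatives and false positives are both 0.

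- Sensitivity = TP / (TP + FN): estimable among classified cases.
- Specificity = TN / (TN + FP) = 0/0: undefined at any N.
- Positive predictive value = TP / (TP + 0) = 100% for any marker with at least one positive result: uninformative.
- Negative predictive value = 0 / (0 + FN) = 0% if any case tests negative: uninformative.

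Manifestations at onset are recorded (section 2.4), so onset features can be described. Early organ damage within SLE can also be studied.

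**The case against.** **Direction is not shown.** A reader might infer that the rates will certainly be tilted towards severe disease. The documents do not go that far. The centre criteria also include a dedicated outpatient clinic and a cohort under regular follow-up, which fit routine long-term care. Non-consent or loss of very ill patients could act the other way. Some text makes over-representation of severe disease plausible: the Discussion says that patients likelier to receive new treatments are often more treatment-resistant, and access to such drugs is a centre criterion. That is an argument for plausibility, not evidence. This part of the objection stands.

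**The denominator exists.** The outcome is the frequency of manifestations among SLE patients, not of SLE among Italians, so no general-population denominator is needed. This is correct. The remaining question is which SLE patients the denominator represents.

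**The biomarker objective promises no specificity.** A reader might conclude that the whole objective is out of reach. It is not: sensitivity among cases, onset features and treatment guidance remain open, and a later registry study could add comparators. The cohort as described still cannot show how a marker performs in diagnosing SLE.

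**The bias claim may concern measurement.** The sentence begins with standardised data collection, and section 2.7 sets out real quality controls. Read that way the claim is more defensible, but the text does not restrict it to measurement, and the power claim gains nothing from that reading.

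**Conclusion.** The mismatch between target and frame stands on the article's own text. The primary rates will describe adults with classified SLE followed at participating referral centres, and they may differ from national values in either direction. The size is unknown: the tabulated figures rest on assumed p and r and show only that modest selection can move a prevalence by several points and that enrolling more patients does not correct it. A statement that the registry will overstate severe disease by a given number of points is not supported.

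The unqualified bias claim and the power claim in the Conclusions lack support. For biomarkers, the limit applies to specificity and predictive values for diagnosing SLE and holds at any sample size. It does not extend to sensitivity among cases, onset features or early organ damage within SLE. These points should be corrected because they change what the registry may conclude; they do not undermine its value as a referral-centre cohort.

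**What to change.** 1. In the aim, the specific objectives and the primary-outcome paragraph of the Introduction, and in the Conclusions, restate the target population as adults with classified SLE followed at participating LUNET referral centres.
2. In the Conclusions, delete the power claim or make it conditional on the later sample-size work, and delete the bias claim or restrict it to measurement.
3. Limit the biomarker objective to early identification of organ involvement, activity and prognosis within established SLE.
4. If not already captured (the full variable list is in Figure 3, which is not shown), record residence and the origin and reason of referral at enrolment. Report the primary prevalences in local residents as a sensitivity analysis. Local residents are still patients of a specialist centre, so this probes geographic referral only and does not recover a national figure.

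The first three changes are wording. The fourth adds minor data entry and one extra tabulation. The price is a less ambitious claim.

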## 2. Materials and Methods

### 2.1. Registry Design and Governance

The LUNET registry will adopt a multicenter observational prospective methodology designed to create a network of reference centers with specific expertise in managing SLE patients, with the aim of compiling the most comprehensive possible data on the clinical, laboratory, and instrument-measured characteristics of this disease in a real-world setting. To meet this objective, an extensive database of patients with SLE, according to SLICC 2012 [1] and/or ACR/EULAR 2019 [2], will be established and analyzed to gain insight into various clinically and scientifically relevant aspects of SLE.

This study is promoted by the Italian Society of Allergy, Asthma, and Clinical Immunology (SIAAIC), which was founded in 1953, and is the largest Italian scientific society dedicated to allergy and clinical immunology. The SIAAIC has about 1800 active members affiliated with universities, hospital departments, and territorial outpatient clinics. Its main aim is to advance allergy and clinical immunology as a discipline via integrated efforts in specialist and post-specialist education, promotion of knowledge in this field, the conduct of clinical and epidemiological research, and support of patient organizations (https://siaaic.org/; accessed on 13 March 2025).

### 2.2. Oversight

The LUNET Study is overseen by three governing bodies: the LUNET Steering Committee (SC), the LUNET Scientific Committee (SciC), and the Publication and Dissemination Committee (P&DC) (Figure 1).

The LUNET Network currently comprises 18 centers across Italy, and involves leading experts in clinical immunology, internal medicine, and rheumatology (Figure 2).

The LUNET Network remains open to the inclusion of additional centers to continuously expand the dataset and improve the representativeness of its real-world clinical evidence. The primary requirement for participating centers is a specific expertise in diagnosing and managing SLE patients. Specific selection criteria include: access to an active cohort of patients with SLE sufficient to ensure regular enrollment and follow-up; availability of qualified personnel such as clinical investigators and research nurses; a dedicated outpatient clinic for systemic autoimmune diseases; access to biotechnological and investigational drugs; Day Hospital/Day Service activities; ward support for standard inpatient admissions and/or dedicated beds; and availability of instrumental diagnostics (e.g., capillaroscopy, spirometry, ultrasound, renal biopsy, etc.).

